### Sample size and recruitment

The sample size was determined based on the sample size calculated for the previous randomized clinical trial, which was based on Curtis et al. [42]. We decided to use the mentioned study, even though it is on adults, as it is one of the very few available studies that deals with the management of caries using an updated system, similar to CariesCare International, taking into consideration both the care of caries lesions according to their severity and activity status, as well as of the individual caries risk. The results show differences in averages of surfaces with caries progression, between two preventive care schemes. The Whitehead sample size calculation formula was taken into account, with type-I error: 0.05, type II error: 10%, standard deviation 2.5, expected average of the first group 1.3 and expected average of the second group 2.1.

For the current study, as there is no control arm, with the leader team it was decided to include half of the previous RCT sample size. Thus, the sample size calculation of this single-group interventional study corresponded to 206 3–5 and 6–8 years old children, increasing to a total of 258 after including a 25% dropout. As the sample calculation per arm in each centre in the previous study corresponded to 20 participants, in this single-interventional study we are asking each centre to recruit 27 patients. These would correspond to 567 participants in total if the centres [21] finish the study with 27 participants each.

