### Statistical analysis plan

All the baseline and follow-up the individual- and tooth-level data, the parents’ and dentists’ TEI data, and costs’ information will be digitally registered (after training) for each codified patient in each centre keeping data safely stored and with limited access, in a designed data base in Microsoft Excel (2010), that includes data quality assurance by validation of data. The data will be sent to the DMT at each time point. Data will be analysed by an independent statistician. All statistical tests will be two-tailed tests. The level of statistical significance for all two-sided tests will be set at 0.05. Parametric methods will be considered first. Data that do not meet or cannot be transformed to meet parametric assumptions will be analysed by non-parametric methods. Demographic and clinical features of the participants (centre, gender, age, caries risk, pain, filling status, prs/PRS); oral health behaviour, dental care acceptability and costs, as well as caries experience (DMFS and dmfs with the D component using ICDAS-merged Epi) [35] will be described using mean and standard deviation (SD) for quantitative variables and percentages for qualitative variables.

Regarding costs, the providers’ payment model of the centre will be described (Fee-for-service, Capitation, Salary-based and Pay-for-performance) [43]. For the description of costs, these will be converted to the United States Dollar (USD) under the average Market Representative Exchange Rate for the year 2021 (MRER-average).

ANOVA and Kruskal Wallis analyses will be used to compare the baseline characteristics between centres.

The caries risk control (subjects where risk was reduced from high risk or maintained in low risk), and the number of subjects with avoidance of extraction, pain, and failure of restorations/sealants, will be compared between baseline (T0) and 12-month follow-up (T3) examinations using χ^2^.

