## Discussion

This is a multicentre single-group intervention study that will assess the caries-control effectiveness of CCI adapted for the pandemic outcomes in children. While the previous proposal for the study was a RCT which would compare CCI with standard care, the COVID-19 pandemic obliged a change of plan for this study to only one intervention group and to test an adapted CCI, without AGP and reduced in-office appointments’ time. Children have the right to receive an effective dental care even during the pandemic [16, 44, 45]. The CCI system is a comprehensive caries care system focused in improving oral health outcomes through a patient-centred risk-based friendly management for the practice [9]. The proposed care options have been recognised as effective for caries care [4–7, 24–27, 30, 33, 34, 36, 46] and most have been proposed as being suitable for this pandemic era [16–22], as have teledentistry and other patient’s remote communication means [16–18, 22, 23]. The short behaviour change tool helps in the management of caries risk by linking the patient as an active actor to improve oral health habits [29, 30]. Given the characteristics of the proposed adapted-CCI system, we will explore the effectiveness control of caries progression at both tooth-surface and individual-level, oral-health behaviour improvement, and parents’ and dentists’ process acceptability. If the results are positive, this will help to change the standard of care during the pandemic and beyond it. Results will be widely available to increase the translation and adoption of CCI in other countries, as well as contribute to the evidence in the use of non-AGP and remote appointments during the pandemics.

Compared to other childhood diseases, caries in both the permanent and the primary dentition is highly prevalent (1st and 12th, respectively) (1). Additionally, disease rates are higher in young children and schoolchildren in low- and middle-income populations. In deciding which age groups to study we considered 3–5 and 6–8 years old children to be important particularly due to changing diet and lifestyles, as well as the additional caries risk that the eruptive first permanent molar teeth pose [47, 48].

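### The 206 children are one arm of a two-arm power calculation, so the 10% type II error behind that number belongs to no analysis in this single-group study

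*Protocol article*

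**What the plan says.** Sample size and recruitment gives the inputs of the earlier randomised trial: "type-I error: 0.05, type II error: 10%, standard deviation 2.5", "expected average of the first group 1.3 and expected average of the second group 2.1". They come from a study in adults that compared surfaces with caries progression under two preventive care schemes. The section then says: "as there is no control arm, with the leader team it was decided to include half of the previous RCT sample size". The resulting 206 is called the calculation of the present single-group study. It becomes 258 after a 25% dropout allowance. Separately, each of 21 centres is asked for 27 children, 567 in all.

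Under Outcomes, the primary outcome is a mean per-child count of surfaces in which progression was avoided. No reference value is attached.

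The Statistical analysis plan section sets the test level ("The level of statistical significance for all two-sided tests will be set at 0.05") and lists:
- a descriptive analysis of progression;
- a paired Wilcoxon or t test of the number of active lesions at 12 months against baseline;
- a multilevel logistic regression for associations;
- χ² comparisons of T0 with T3 for risk control, extraction, pain and restoration or sealant failure;
- t tests for parents' acceptability and for oral-health behaviour.

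The Discussion concedes that comparability with a control group is lost. It also says: "If the results are positive, this will help to change the standard of care during the pandemic and beyond it".

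**The concern.** A type II error is a property of a particular test. The one quoted belongs to a comparison of two groups, each of the calculated size. Once the second group is removed, keeping the other half of the children does not keep the error rate, because the test has gone too. What remains is a number with no stated link to anything the study will estimate or test.

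Two things are at stake. A reader of the sample-size section may credit the study with error control that it does not have. And the Discussion ties a possible change in the standard of care to a positive result, while the only error rates in the sizing text come from a design that was abandoned.

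**Working it through.** **Inputs.** From Sample size and recruitment: α = 0.05, type II error 10% (power 0.90), SD 2.5, difference 2.1 − 1.3 = 0.8. Two-sided testing is from the Statistical analysis plan section. Equal allocation in the earlier trial is assumed, because exactly half was kept.

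**Reproducing 206.** Per arm, n = 2 × [SD × (z₀.₉₇₅ + z₀.₉₀) / difference]² = 2 × [2.5 × (1.960 + 1.282) / 0.8]² = 205.2, so 206. The t-based version gives 206.2. A one-sided test would give 168, which does not match. So 206 is the size of one arm, and the power at that size (90.1%) requires a second arm of 206, 412 in total.

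**Does any planned analysis use these inputs?**

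| Planned analysis | Tests the 0.8 difference? |
|---|---|
| Description of progression | No test |
| Paired T0–T3 comparison of active-lesion counts | No; different variable, not used for sizing |
| Multilevel logistic regression | No; associations |
| χ² comparisons, T0 against T3 | No; child-level proportions |
| t tests of acceptability and behaviour | No; different variables |

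**How far the 10% depends on the test.** These are illustrations only, using SD 2.5 and a difference of 0.8:
- One-sample test against a fixed value: n = [2.5 × 3.242 / 0.8]² = 102.6, so 103. At 206 the power is Φ(0.8 / (2.5/√206) − 1.96) = Φ(2.63) = 99.6%.
- Paired test, SD of differences = 2.5 × √[2(1 − ρ)], assumed ρ of 0, 0.3, 0.5 and 0.7: n = 206, 144, 103 and 62. Power at 206 is 90.1%, 97.3%, 99.6% and over 99.9%.

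The agreement at ρ = 0 is arithmetical; the protocol makes no such assumption.

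**What the size does fix: precision.** Half-width = 1.96 × 2.5 × √(DE/n), with DE = 1 + (n/21 − 1) × ICC. The centre ICC is an assumption; the protocol gives none.

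| Children completing | ICC 0 | ICC 0.01 | ICC 0.05 | ICC 0.10 |
|---|---|---|---|---|
| 206 (9.8 per centre) | ±0.34 | ±0.36 | ±0.41 | ±0.47 |
| 567 (27 per centre) | ±0.21 | ±0.23 | ±0.31 | ±0.39 |

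**Which variable this applies to.** The SD and the two means concern surfaces with progression. The primary outcome counts surfaces with avoidance of it. For one child, surfaces avoided = surfaces assessed − surfaces progressed. Its spread therefore also depends on how many surfaces each child contributes, and 2.5 does not carry over. The half-widths above describe mean progressed surfaces per child, and only if the adult SD holds in children.

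**The case against.** Four replies have weight.

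*The protocol does not claim 90% power for the single-group study.* This stands. The "type II error: 10"% figure is given for the earlier trial's formula, and the halving is openly described as a decision. A reader might infer that the article promises 90% power for this study; it does not say so. What it does is call the product of that formula this study's calculation, and that label is wrong.

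*There is inference within the group.* This also stands. The paired test of active lesions and the χ² comparisons are real tests at the 5% level, and activity is part of the definition of progression. But none of them is a test of the primary outcome, and none was used for sizing.

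*A success criterion may be in the full analysis plan.* It may. Data Availability says that such a plan can be requested, and it is not shown here. A reader might infer that a positive result has no criterion anywhere, or that the trial cannot answer its question. The article alone cannot establish either. The sizing rationale, however, is stated in the article.

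*The claims are hedged and the single arm was forced.* The Discussion speaks of exploring effectiveness and admits the loss of the control group. That explains the design, but it leaves the sizing statement and the standard-of-care sentence as they are.

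Two further inferences should be resisted. One is that the study is too small: in the illustrations above 206 is as many as needed or more, and 567 children are sought. The other is that 2.1 could serve as a success threshold. It is the second-group mean from an adult study, on the opposite outcome direction, and the article gives neither its follow-up time nor its definition of progression. Using it would be an uncontrolled historical comparison.

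**Conclusion.** The point holds as a defect of rationale. The figure of 206 is exactly the per-arm size of a two-arm comparison, and the 10% type II error attaches to no analysis in this protocol. No corrected number follows, because the article gives no reference value, margin or target precision for the single group, and no shortage of children is shown.

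What the size can support is an estimate of mean progressed surfaces per child to within about ±0.34 at 206 completers, or ±0.36 to ±0.47 allowing for centres. At 567 this is ±0.21, or ±0.23 to ±0.39. These figures rest on the adult SD of 2.5 applying to children, on 21 equally filled centres, and on the assumed ICC range of 0.01 to 0.10. They do not describe the primary outcome as it is worded.

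**What to change.** In Sample size and recruitment:
- State that the 206 came from the two-arm trial and that its type I and type II errors do not apply to the single-group study.
- Justify the size as precision, giving the half-widths at 206 and 567 with and without the centre adjustment. Label the SD as borrowed from adults and the ICC range as assumed.
- State that the inputs concern surfaces with progression, whereas the primary outcome is worded as surfaces with avoidance of it.

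Present the 12-month result as a single-group estimate with its 95% confidence interval. Limit the Discussion sentence so that no effectiveness or standard-of-care claim rests on an uncontrolled positive result. Do not adopt 2.1 as a threshold.

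The cost is a rewritten sample-size section and one Discussion sentence. No further children, visits or data are needed. The downside is a more modest claim.

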**Methods:**

In this 1-year multi-centre single-group interventional trial the adapted-CCI effectiveness will be assessed in one single group in terms of tooth-surface level caries progression control, and secondarily, individual-level caries progression control, children’s oral-health behaviour change, parents’ and dentists’ process acceptability, and costs exploration. A sample size of 258 3–5 and 6–8 years old patients was calculated after removing half from the previous RCT, allowing for a 25% dropout, including generally health children (27 per centre). The single-group intervention will be the adapted-CCI 4D-cycle caries care, with non-AGP and reduced in-office appointments’ time. A trained examiner per centre will conduct examinations at baseline, at 5–5.5 months (3 months after basic management), 8.5 and 12 months, assessing the child’s CCI caries risk and oral-health behaviour, visually staging and assessing caries-lesions severity and activity without air-drying (ICDAS-merged Epi); fillings/sealants; missing/dental-sepsis teeth, and tooth symptoms, synthetizing together with parent and external-trained dental practitioner (DP) the patient- and tooth-surface level diagnoses and personalised care plan. DP will deliver the adapted-CCI caries care. Parents’ and dentists’ process acceptability will be assessed via Treatment-Evaluation-Inventory questionnaires, and costs in terms of number of appointments and activities. Twenty-one centres in 13 countries will participate.

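### The 258 said to allow for 25% dropout from 206 covers only about 20% (275 is needed), and its relation to the 567 implied by 27 per centre is not stated

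*Protocol article*

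**What the plan says.** The section on sample size and recruitment in the protocol article starts from the earlier randomised design, "with type-I error: 0.05, type II error: 10%, standard deviation 2.5", and expected group means of 1.3 and 2.1. Half of that trial's size is carried over to the single-group study, giving 206 children, "increasing to a total of 258 after including a 25% dropout".

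The section then moves to a per-centre request: "As the sample calculation per arm in each centre in the previous study corresponded to 20 participants", each centre is now asked to recruit 27. It closes with a second total: "These would correspond to 567 participants in total if the centres [21] finish the study with 27 participants each".

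The Methods paragraph of the abstract gives 258 as the calculated sample size, "allowing for a 25% dropout, including generally health children (27 per centre"), and ends with 21 centres in 13 countries. It does not mention 567.

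**The concern.** A dropout allowance is meant to leave the required number of children after losses. The losses are a share of those enrolled, so the required number has to be divided by the share retained. Multiplying by one plus the dropout rate always falls short, and 258 looks like the product of that multiplication.

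The section also leaves two totals side by side, 258 and 567, without saying how they relate. A reader of the abstract sees 258, 27 per centre and 21 centres together and cannot make them agree. Finally, 27 is the number each centre recruits in one sentence and the number it finishes with in the next. Both can be true only if nobody drops out, yet the same section plans for a quarter to leave.

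At stake is whether the trial can later show that it met its planned size. The Discussion admits that centres' start, conduct and finish dates are uncertain, so uneven recruitment is foreseeable and the minimum acceptable number matters.

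**Working it through.** **Inputs.** From the sample size section: type I error 0.05, type II error 10%, standard deviation 2.5, means 1.3 and 2.1 (difference 0.8), required number 206, dropout 25%, enrolment 258, request of 27 per centre. From the abstract and the Methods/design section: 21 centres. The sample size section does not give sidedness; the statistical analysis section says "All statistical tests will be two-tailed tests", so two-sided is used.

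**1. Reproduce 206.** For two means, n per arm = 2 × (z for 0.975 + z for 0.90)² × SD² / difference² = 2 × (1.960 + 1.2816)² × 6.25 / 0.64 = 205.2, rounded up to 206. This matches. A one-sided test gives 168 and does not.

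**2. Reproduce 258.** 206 × 1.25 = 257.5, rounded up to 258. This matches.

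**3. What 258 leaves.** 258 × (1 − 0.25) = 193.5, so about 193 completers, roughly 12 below 206.

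**4. What 25% dropout requires.** 206 / (1 − 0.25) = 274.7, rounded up to 275. Check: 275 × 0.75 = 206.25. The stated figure is 275 − 258 = 17 short.

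**5. What dropout 258 does cover.** 1 − 206/258 = 52/258 = 20.2%.

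**6. The per-centre request.** 27 × 21 = 567, as printed. 567/258 = 2.2. Spread over 21 centres, 258 is 258/21 = 12.3 per centre; at 27 per centre it is reached with 258/27 = 9.6 centres.

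**7. Recruiting against finishing.** If 27 per centre are recruited and 25% leave, 567 × 0.75 = 425 finish, about 20 per centre. The printed sentence describes 567 finishing.

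**The case against.** The strongest reply is that the two faults largely offset each other. The only operational instruction is that each centre recruit 27, and nothing says that recruitment stops at 258. If all 21 centres comply, about 425 children complete. Even if only 11 centres filled their quota, 11 × 27 = 297 enrolled would leave 297 × 0.75 = 223, still above 206. This stands, and it is why the matter is less than critical. It does not make 258 correct for the dropout it claims to cover.

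A second reply is that 567 is printed openly and conditionally, so 258 can be read as a calculated minimum and 567 as the yield if every centre delivers. That is a sensible reading, and it rules out a charge of a hidden multiplication error. But the article does not state it, and the abstract leaves 567 out. A third reply, that *finish* is loose wording because the preceding sentence says recruit, is fair; that part is editorial.

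Three stronger inferences are tempting but not supported:

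- A reader might multiply the earlier trial's 20 per arm per centre by 21, get 420 against 206, and conclude that 20 was really the figure for both arms and that the quota has been doubled. This assumes that the earlier trial had 21 centres. The Background says only that a number of institutions had been recruited. With 10 or 11 centres, 206/20 = 10.3 and the figure fits as written.
- A reader might say that the section applies two dropout rules, because 20/0.75 = 26.7 rounds up to 27 while the total uses 1.25. The section does not say how 27 follows from 20, nor that it includes dropout. A numerical fit does not show the method.
- A reader might express the shortfall as lost power. The formula behind 206 describes a comparison of two arms, which this trial does not make, so a power figure from it says nothing about the single-group analysis.

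**Conclusion.** Wrong as written, and it should be fixed. The enrolment of 258 does not keep 206 completers at the stated 25% dropout: it leaves about 193, covers only about 20% dropout, and is 17 children below the 275 needed. Separately, the article does not say whether 258 or 567 is the target, and it uses 27 for both recruited and finishing children.

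The conclusion takes 206 as the number of children meant to complete, and the 25% as a share of those enrolled, which is the ordinary meaning of a dropout rate. If the authors meant simply to add 25% to 206, the arithmetic is theirs to choose, but the result should not be described as covering 25% dropout. The figure of 275 only carries 206 forward correctly; it does not show that 206 is the right number for a single-group study. The shortfall matters only if recruitment ends near 258, and disappears if the centres recruit 27 each.

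**What to change.** In the abstract and in the sample size section, replace 258 with 275, or keep 258 and say that it covers about 20% dropout.

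State how the totals relate. If the intention is a minimum plus a margin, say that 275 is the calculated minimum enrolment for 206 completers, and that 27 per centre in 21 centres is the recruitment request: 567 enrolled and about 425 completers at 25% dropout. If a single target is intended, name it. Give the same statement in the abstract, where 567 is now absent.

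In the last sentence of the sample size section, change *finish* to *recruit*, so that 27 has one meaning.

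The cost is a few sentences. No children are needed beyond the 27 per centre already requested, and no analysis changes.

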### Statistical analysis plan

All the baseline and follow-up the individual- and tooth-level data, the parents’ and dentists’ TEI data, and costs’ information will be digitally registered (after training) for each codified patient in each centre keeping data safely stored and with limited access, in a designed data base in Microsoft Excel (2010), that includes data quality assurance by validation of data. The data will be sent to the DMT at each time point. Data will be analysed by an independent statistician. All statistical tests will be two-tailed tests. The level of statistical significance for all two-sided tests will be set at 0.05. Parametric methods will be considered first. Data that do not meet or cannot be transformed to meet parametric assumptions will be analysed by non-parametric methods. Demographic and clinical features of the participants (centre, gender, age, caries risk, pain, filling status, prs/PRS); oral health behaviour, dental care acceptability and costs, as well as caries experience (DMFS and dmfs with the D component using ICDAS-merged Epi) [35] will be described using mean and standard deviation (SD) for quantitative variables and percentages for qualitative variables.

Regarding costs, the providers’ payment model of the centre will be described (Fee-for-service, Capitation, Salary-based and Pay-for-performance) [43]. For the description of costs, these will be converted to the United States Dollar (USD) under the average Market Representative Exchange Rate for the year 2021 (MRER-average).

ANOVA and Kruskal Wallis analyses will be used to compare the baseline characteristics between centres.

The caries risk control (subjects where risk was reduced from high risk or maintained in low risk), and the number of subjects with avoidance of extraction, pain, and failure of restorations/sealants, will be compared between baseline (T0) and 12-month follow-up (T3) examinations using χ^2^.

For the analyses at the tooth-surface level, we will exclude teeth that needed a treatment involving AGP (endodontic treatment, surgical extraction, etc.). Caries progression has been defined for this study in terms of a change from the decided and delivered tooth-surface level care (T0, after the 4D basic management) to the tooth-surface level status at the 12-month follow-up (T3) (Fig. 2), as follows: (1) from a sound surface to a caries lesion, a sealant, a filling, or a missing tooth; (2) from a sealant to a caries lesion, a filling, or a missing tooth; (3) to a more severe caries score and/or an active status (or remaining active), and (4) from a filling to a caries lesion or a missing tooth. The severity/activity caries progression will be firstly assessed through descriptive analyses (number of subjects/surfaces) and a comparison in the number of active lesions at 1 year versus baseline will be applied (Wilcoxon test or paired *t* test based on results of the Shapiro Wilk normality test). Multilevel logistic regression will also be used for the surface level data analyses, exploring the clustering of surfaces within individuals, to estimate the association among characteristics variables and the outcomes.

Parents’ treatment evaluation inventory: Comparisons of parents’ treatment acceptability will be conducted between participants classified in baseline as low vs. high risk using Independent *t* test.

Dentists’ treatment evaluation inventory: The dentists’ treatment acceptability will be described.

Oral-health related behaviour classification will be compared between assessments (T0, T1, T2, T3) and between high and low-risk patients using *t* test.

The level of significance considered for all tests will be 5%.

Analyses to handle protocol non-adherence and missing data: Data of patients who leave before the end of the study will be handled separately. A *t* test analysis will be conducted to compare the baseline mean number of surfaces with caries experience (ICDAS-merged Epi dmfs/DMFS) [35] of those children who left the study during the 1-year follow-up period with that of those who remained in the study. If they’ve left after T1 and or T2, their parents TEI will be also compared with that of those who remained, as well as the children’s oral-health behaviour classification, and the caries progression.

Oversight and monitoring: Throughout the study virtual meetings will be held to solve any adverse situation and to resolve any issues or concerns about the study protocols.

Adverse events and harms: There is a minimal risk of participating in this study, similar to that of routine dental care. All procedures involved have scientific support and are part of best clinical practices. Disposable materials and sterilized instruments will be used. Adverse events, if any, will be recorded and reported to the Coordinating Centre. Its management will follow dental clinics’ guidelines.

Auditing: The centres’ coordinators will be reporting any protocol deviation and updating periodically to the Endpoint Adjudication Committee. The Study Steering Committee will periodically audit the general conduction of the study. The Coordinator Centre will periodically audit the centres by assessing the data bases of a number of subjects independent from the centre dental team. The audit processes are independent from the sponsor.

Protocol amendments: According with the Research Institutional Ethical Committee in Universidad El Bosque, any modification to the project or to the approved forms must be submitted to them for its approval.

